#### Pediatric *Tuina* group

Participants will receive pediatric *Tuina* treatment for 20 min each session. Once 2 days for four times. Treatment will be performed with the child lies in bed, with the placate by parents or legal guardians at the bedside. The standard pediatric *Tuina* includes 7 acupoints, which are determined by the literature review [27], and the pediatric *Tuina* professor with 30 years’ experience. Manipulation times is depended on the children’s age. Detailed information of acupoints, manipulation methods, and times is provided in Table 2. The location of acupoints and manipulations are shown in Additional file 2. The manipulations are light, fast, and gentle.

**Table 2 Tab2:** Acupoints, manipulation methods and times

Age	Times							
	Large intestine meridian, reducing, pushing	Lung meridian, reducing, pushing	*Liufu*, reducing, pushing	*Sanguan*, reinforcing, pushing	Abdomen, clockwise, rubbing, and vibration	*Tianshu*, vertical, pressing, and vibration	*Qijiegu*, downward, pushing	*Guiwei*, clockwise, rubbing
≥ 1 year old and < 4 years old	300	200	200	20	300	300	300	200
≥ 4 years old and < 7 years old	500	400	400	40	500	500	500	400

#### Medilac-Vita group

According to the guideline of the Chinese Preventive Medicine Association (CPMA) in 2017, probiotics such as Medilac-Vita are recommended for the treatment of FC in children [28]. Participants assigned to this group will receive probiotics treatment. Medilac-Vita (combined bacillus subtilis and *enterococcus faecium* granules with multivitamins, live), which has been widely used for FC in children [29–32]. Participants will take 1 g (1 to 4 years old) or 2 g (4 to 7 years old) Medilac-Vita (Hanmi Pharm Co., Ltd., Beijing, China) dissolved in 100 ml water (40 °C), according to the drug instruction (Additional file 3). Twice a day, 7 consecutive days in total. After the treatment period, parents or guardians of the participants will be required to return any untaken drugs to avoid adverse consequences for follow-up.

### Outcomes measurement

A printed or electronic case report form (CRF) with the random number for each participant will be used to record all information. Three assessors who are blind to the group allocations will collect the basic information and assess the outcomes every week from the baseline to the end of follow-up. The first one will assess outcomes from the Second Affiliated Hospital of the Yunnan University of Chinese Medicine, Yunnan Province Hospital of TCM, and Kunming Children’s Hospital. The second one is for Zhejiang Provincial People’s Hospital. The third one is for Shandong Province Hospital of TCM.

#### Stool diary

Parents or legal guardians are required to keep a stool diary from baseline to intervention period and follow-up period. The stool diary contains 5 domains: weekly spontaneous bowel movements (SBMs), weekly complete spontaneous bowel movements (CSBMs), stool form, distress sensation, and glycerine enema rate.

#### Primary outcomes

The primary outcomes are weekly SBMs and/or CSBMs. Children older than 4 years old could answer whether defecation is complete. The assessors will check the stool diary and gather the data from baseline until the end of the follow-up.

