**Methods/design:**

This study is a randomized, controlled, multicentre, clinical trial. We will include 176 children with FC from five hospitals. The participants will be randomly allocated into two groups: the pediatric *Tuina* group and the Medilac-Vita group. This study will include a 1-week actual treatment period and a 2-week follow-up period. Primary outcomes are weekly spontaneous bowel movements and weekly complete spontaneous bowel movements. The secondary outcomes are effective rate, stool form, distress sensation, and glycerine enema rate. The assessment will be performed each week. Adverse event will be monitored in the treatment period and follow-up period.

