## Methods/design

### Study design

This study is a prospective, randomized, multicentre, controlled design, and it will be conducted from December 2021 to December 2024. We will recruit 176 participants from 5 hospitals in 3 different provinces (Yunnan province, Zhejiang province, and Shandong Province). The eligible participants will be randomly allocated to 2 groups in a 1:1 ratio. The randomization sequence will be computer generated by the Clinical Research Center of the Yunnan University of Chinese Medicine. Every participant will receive a 1-week treatment period and a 2-week follow-up. Basic information and outcomes will be assessed at baseline and after each week. The flowchart is shown in Fig. 1, and the schedule is shown in Table 1.

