### Data collection

In this study, an independent data administrator will collect data every 3 months, from three assessors. The data of each participant includes basic information and outcomes. The basic information includes the participant’s gender, age, height, weight, history of pregnancy and delivery, past medical history, present condition, phone, and WeChat number of parents or legal guardians. Outcomes will be collected four times from baseline to the end of follow-up.

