### Statistical analysis

The statistician will perform statistical analysis by using SPSS 19.0 statistics software (IBM Co., Armonk, NY, USA) and GraphPad 7.04 statistics software (GraphPad Software Co., San Diego, California, USA). Continuous variables are presented as the mean and standard deviation (SD). While the nonnormally distributed variables are presented as the median and interquartile range (IQR). Categorical variables are described as numbers and percentages (%).

Before the comparison, the normality and homogeneity of variance will be tested. Normality of continuous variables (SBMs, CSBMs, m-BSFS, distress sensation, and glycerine enema rate) will be determined by *Shapiro-Wilk* test, *Kolmogorov-Smirnov* test, *Skewness*, and *Kurtosis*. Homogeneity of variance of continuous variables will be determined by *F* test, *Brown-Forsythe*, and *Bartlett’s* test. Independent-Sample *t*-test or nonparametric test (*Mann-Whitney* test) will be used when compared between two groups. Paired *t*-test or nonparametric test (*Wilcoxon* test) will be performed to compare within a group. For the categorical variables (effective rate), the *χ*^2^ test will be performed to evaluate the significance of the difference. The statistical analysis will be a 2-sided test with a significance level of 0.05.

The missing data were will be dealt with expectation maximization, last observation carried forward method or listwise deletion. Subgroup analysis will be conducted according to the subject’s age (< 4 years and ≥ 4 years), which depends on the normality and homogeneity of variance of the data.

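### Two primary outcomes at three weekly assessments, with no primary week and no success rule, leave up to six comparisons at two-sided 0.05 from which the headline result could be chosen

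*Protocol article*

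**What the plan says.** The Primary outcomes section of the protocol article states: "The primary outcomes are weekly SBMs and/or CSBMs". The next sentence adds: "Children older than 4 years old could answer whether defecation is complete". The abstract puts it differently: "Primary outcomes are weekly spontaneous bowel movements and weekly complete spontaneous bowel movements".

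On timing, the Study design section says: "Basic information and outcomes will be assessed at baseline and after each week". The Data collection section says: "Outcomes will be collected four times from baseline to the end of follow-up". In Table 1 the four occasions are day 0 and days 7, 14 and 21. Treatment runs over days 0 to 6, so day 7 closes the treatment week, and days 14 and 21 fall in the two-week follow-up. No occasion is singled out as primary.

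In the Statistical analysis section, an independent-samples t-test or Mann-Whitney test "will be used when compared between two groups", and "The statistical analysis will be a 2-sided test with a significance level of 0.05". The section describes no alpha split, testing order, both-must-succeed rule or model that combines the weeks.

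**The concern.** The 0.05 level holds for a single comparison fixed in advance. Here the primary claim, that Tuina is more effective than the probiotic, can rest on SBMs or CSBMs and on day 7, 14 or 21. These are also different questions: day 7 concerns the effect over the treatment week, while days 14 and 21 concern its persistence off treatment. With nothing fixed, the outcome and week to be headlined could be selected after the results are known, and the stated significance level would then no longer describe the chance of a false positive. The Discussion hopes the trial will support clinical guidelines and insurance coverage, so the decisive comparison should be identifiable beforehand.

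**Working it through.** **Can the sample size identify the decisive comparison?** The plan's own figure reproduces. In degrees, arcsin√0.90 − arcsin√0.70 = 71.57 − 56.79 = 14.78, and n = 1641.4 × (3.242/14.78)² ≈ 79.0 per group (79.02 with unrounded angles, as stated). Then 79/0.9 = 87.8, rounded up to 88 per group and 176 in total. This calculation uses the effective rate, which the protocol lists as secondary, so it does not show which primary comparison decides the trial.

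**Number of comparisons.** 2 outcomes × 3 post-baseline weeks = 6.

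**Independent tests at 0.05 each.** The family-wise error is 1 − 0.95^k:
- k = 6: 1 − 0.95⁶ = 26.5%
- k = 3 (one outcome, three weeks): 1 − 0.95³ = 14.3%
- k = 2 (both outcomes, one week): 1 − 0.95² = 9.75%

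**Correlated tests.** The six comparisons are correlated, but the documents give no correlations, so these are assumptions. Six two-sided z-tests were simulated (400,000 draws per setting) with no true difference anywhere. The correlation between weeks within an outcome was varied from 0 to 0.9, and that between outcomes in the same week from 0.3 to 0.9. The correlation across both is their product. The share of children able to report completeness is also not given, so CSBMs were taken as available in all children or in half. With half, the between-outcome correlation is multiplied by √0.5.

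| Correlation (weeks / outcomes) | Any of six, CSBMs in all | Any of six, CSBMs in half | Any of six favouring Tuina, CSBMs in all | One outcome, three weeks | Both outcomes, one week, CSBMs in all |
|---|---|---|---|---|---|
| 0.3 / 0.3 | 24.8% | 25.2% | 12.7% | 13.6% | 9.5% |
| 0.5 / 0.5 | 21.9% | 22.7% | 11.0% | 12.5% | 9.0% |
| 0.7 / 0.7 | 17.7% | 19.2% | 8.9% | 10.9% | 8.4% |
| 0.8 / 0.8 | 14.8% | 17.0% | 7.4% | 9.8% | 7.7% |
| 0.9 / 0.9 | 11.5% | 14.1% | 5.8% | 8.4% | 7.0% |

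Over all settings tried, any-of-six runs from 11.5% to 26.3%. Counting only errors in Tuina's favour, it runs from 5.8% to 13.9%, against 0.05/2 = 2.5% for one planned test.

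**Error under a fixed rule.** One named outcome at one named week gives 5%. A Bonferroni split over six tests (0.05/6 = 0.0083 each) gives 2.3-4.8% overall.

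**The case against.** The strongest reply is that *and/or* is not a success rule. The sentence after it concerns which children can say whether defecation was complete, so the natural reading is SBMs in every child plus CSBMs in those old enough to report them. This is a fair reading, and it largely removes the conflict with the abstract. A reader might infer that the protocol declares success on either outcome at any week. No section says so, and six chances is only the widest reading left open. What remains is that both outcomes are still primary at three unranked weeks. Restricting CSBMs to a subset lowers the correlation and slightly raises the error.

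If both outcomes had to succeed, the inflation across outcomes would go. The choice among weeks would remain, and the error could approach the one-outcome, three-week figure of about 8-14% where the other outcome truly differs.

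A second reply is that this is a condensed article and that testing order may sit in an analysis plan not shown. That is right as far as it goes, and the lack of a multiplicity procedure alone would not be a point. But the outcome definition, including its decisive time, is a matter for the protocol, and the article words it in two ways.

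Third, 15-25% should not be read as the chance of falsely declaring Tuina superior. It counts errors in both directions and rests on assumed correlations. Both limits are accepted.

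**Conclusion.** The point stands as a defect in how the primary comparison is fixed. As written, the plan does not secure 0.05 for the primary claim, because it neither names the decisive outcome and week nor says how the two outcomes combine. If any of the six comparisons counts as success, the family-wise error is about 11-26%, and about 15-25% for correlations of 0.3 to 0.8. For a false claim favouring Tuina it is roughly 6-14% against 2.5%. Settling the outcome but not the week still leaves about 8-14%, and settling the week but not the outcome about 7-10%. All these figures assume no true difference and depend on correlations and a CSBM share that the documents do not give. No setting tried brought the any-of-six rate down to 5%. The documents do not support saying that the protocol has adopted an either-outcome, any-week rule.

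**What to change.** Before any outcome data are compared between groups, replace *and/or* with one named primary outcome at one named time. One workable form is weekly SBMs over the treatment week, assessed at day 7, at two-sided 0.05, since every child contributes and it matches the treatment period. Test CSBMs in the older children only if SBMs are significant, make days 14 and 21 secondary as evidence of persistence, and align the abstract and the registry entry.

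Day-7 SBMs is not the only defensible choice. An alpha split, a both-must-succeed rule at a named week, or one model over the three weeks with a single stated contrast would also control the error if fixed in advance.

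The cost is wording only, with no added children or visits. The Trial status section places the trial in therapist training, but the study dates start in December 2021, so the article cannot show whether recruitment has since begun. The downside is that an effect seen only in follow-up, or only in CSBMs, could no longer be called a primary success.

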#### Secondary outcomes

The secondary outcomes are effective rate, stool form, distress sensation, and glycerine enema rate. The effective rate is the number of participants who are effective (on average, at least one bowel movement in 3 days, stool softening, defecate unobstructed) divided by a total number of the group. Stool form will be measured according to the modified Bristol stool form scale (m-BSFS) (Table 3), which classifies the form of children’s feces into 5 types from separate hard lumps (type 1) to entirely watery (type 5) [33, 34]. Distress sensation measured in the range of 0–3 represents the intensity of distress during defecation, “0” means no cry or grimace, “1” means slight cry and grimace, “2” means medium cry and grimace, and “3” means hysterical cry and grimace. Glycerine enema rate is the times of using glycerine enema divided by the times of defecation, within a week.

**Table 3 Tab3:** Modified Bristol stool form

**Type**	1	2	3	4	5

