### Interventions

To ensure all manipulations follow the standard procedures. The therapists in this trial own an official medical license and hold a master’s degree in pediatric *Tuina*. During this period, participants are not allowed to use any other interventions, at least in principle. If participants take any other interventions in this period, they will be defined as non-adherent and will be dealt with drop out.

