### Sample size

A previous relevant study showed the effective rate of pediatric *Tuina* was 92.5% and Medilac-Vita was 72.5% [35]. Based on our own clinical experience, we consulted pediatric *Tuina* and physician experts. We anticipate an effective rate of 90% in the pediatric *Tuina* group and 70% in the Medilac-Vita group. Considering *α* = 0.05, 1-*β* = 0.90, *p*_1_ = 0.90, *p*_2_ = 0.70, *u*_0.05/2_ = 1.96, *u*_0.1_ = 1.282 [36], $$n=1641.4\times {\left[\frac{\left(1.96+1.282\right)}{\sin \sqrt[-1]{0.90}-\sin \sqrt[-1]{0.70}}\right]}^2$$ = 79.02 ≈ 79. With a drop-out of 10%, 88 FC children will be finally recruited in each group. Totally, 176 participants will be finally recruited in this study.

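### The effective rate's denominator, the drop-out inflation behind 176 children and the open list of missing-data methods do not fit together, so neither the rate nor its power is fixed

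*Protocol article*

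**What the plan says.** Protocol article, Secondary outcomes: the effective rate is the number of effective children "divided by a total number of the group". The section does not say whether this means all randomised or all analysed children, or how a child who has left is classified. In Study design, children are "randomly allocated to 2 groups in a 1:1 ratio", so the ordinary sense of a group there is the randomised arm.

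Protocol article, Sample size: "We anticipate an effective rate of 90% in the pediatric *Tuina* group and 70% in the Medilac-Vita group". The formula gives 79 per group, and then "With a drop-out of 10%, 88 FC children will be finally recruited in each group". No other outcome has a stated power.

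Protocol article, Statistical analysis: missing data are to be handled by "expectation maximization, last observation carried forward method or listwise deletion". No outcome is assigned to any of the three, and no order or criterion is given.

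Protocol article, Drop out criteria and Interventions: reasons for drop-out include withdrawal by parents, other treatment, severe adverse reactions and largely missing diaries. Of children who take other treatment, Interventions says "they will be defined as non-adherent and will be dealt with drop out". Randomization and blinding says that parents cannot be blinded.

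**The concern.** Three sections each settle part of how a drop-out is counted, and they do not agree. Dividing by everyone in the group keeps the child in. Inflating 79 to 88 takes the child out, because the inflation is needed only if drop-outs are not analysed. The list of methods permits either, since listwise deletion leaves about 79 per group and last observation carried forward keeps 88 with an older status.

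Two things are at stake. The first is bias. A child whose constipation is not improving is a likely candidate for other treatment or for withdrawal by an unblinded parent. Deleting that child raises the arm's effective rate, and carrying forward can keep a status that no longer holds. Neither effect need be equal in the two arms, and with three methods open the choice could be made after the data are seen. The second is power. The stated 90% belongs to the version that excludes drop-outs, and the protocol does not commit to that version.

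**Working it through.** **Inputs.** Rates 90% and 70%, z values 1.96 and 1.282, drop-out 10%, 79 and 88 per group (Sample size); "2-sided test with a significance level of 0.05" and a chi-square test for this outcome (Statistical analysis).

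**1. The plan's own figure.** Read in degrees, with the arcsine taken of the square root of each rate:

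n = 1641.4 × [(1.96 + 1.282) / (asin√0.90 − asin√0.70)]² = 79.02, so 79 per group.

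Inflation: 79 / (1 − 0.10) = 87.8, so 88 per group and 176 in total. Both figures reproduce.

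**2. Power formula.** Power = Φ(|asin√p₁ − asin√p₂| × √(2n) − 1.96), angles in radians.

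- Drop-outs excluded, 79 per group, 90% v 70%: 90.0% (pooled chi-square 88.9%, exact enumeration 90.2%).

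**3. All 88 per group in the denominator.** Suppose 90% and 70% hold among completers, 10% drop out of each arm, and a share f of drop-outs is counted effective at the same rates as completers. Then p = 0.9 × rate + 0.1 × f × rate.

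| f | Tuina | Medilac-Vita | Power (arcsine) | Power (chi-square) |
|---|---|---|---|---|
| 0 | 81.0% | 63.0% | 76.8% | 76.2% |
| 0.25 | 83.25% | 64.75% | 81.0% | 80.4% |
| 0.5 | 85.5% | 66.5% | 85.2% | 84.5% |
| 0.75 | 87.75% | 68.25% | 89.2% | 88.4% |
| 1 | 90.0% | 70.0% | 92.8% | 91.9% |

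The f = 0 row is the case in which every drop-out counts as not effective; exact enumeration gives 77.2% there. The f = 1 row gives the same rates as taking 90% and 70% to be whole-group rates from the start.

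**4. One data set, different rates.** Take 88 per group with 79 completers and 9 drop-outs. Completers who are effective: 0.90 × 79 ≈ 71 (Tuina) and 0.70 × 79 ≈ 55 (Medilac-Vita).

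- Listwise deletion: 71/79 = 89.9% v 55/79 = 69.6%.
- All randomised, drop-outs not effective: 71/88 = 80.7% v 55/88 = 62.5%.
- Carrying forward: from those same values up to (71 + 9)/88 = 90.9% and (55 + 9)/88 = 72.7%, depending on each drop-out's last recorded status.

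**The case against.** The strongest reply is that the definition is only the usual description of a proportion. If the group means the children analysed, it agrees with listwise deletion and with the step from 79 to 88. That reading is possible, but the protocol does not state it, and the same Statistical analysis section also permits carrying forward, which keeps drop-outs in. The denominator is therefore open on either reading.

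A second reply is that analysis sets are commonly left to a full protocol or SAP, and that this is a secondary outcome. Silence alone would indeed be no finding. Here, however, the article itself gives a denominator, an inflation premise and a list of methods that do not match, for the outcome on which the whole sample size rests. The secondary status does limit the weight of the point: nothing here concerns the power of the primary outcomes.

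A reader might also infer that the written definition by itself lowers the power to 77%. The document does not support that. The figure needs three things that it does not state: that the group is everyone randomised, that every drop-out counts as not effective (none of the three listed methods sets this as a rule), and that 90% and 70% are completer rates. The anticipated rates are given for each group, so they may already be whole-group rates, and power is then about 93%. The 10% is also not tied to an assessment day. A child lost during follow-up can still have a day 7 result, so the loss at day 7 may be smaller than 10%. Unequal drop-out could move power in either direction, but the document gives no arm-specific rates from which to calculate it.

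**Conclusion.** The inconsistency stands. The protocol does not settle which children form the denominator of the effective rate or how a drop-out is classified, and its sample size assumes one answer that its definition and its list of methods do not secure. Because drop-out is linked to outcome and parents know the treatment, deletion or carrying forward can bias the comparison; the direction and size of that bias cannot be derived from the document.

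The stated 90% power is correct for 79 per group with drop-outs excluded. With all 88 per group in the denominator and an equal 10% drop-out, power lies between about 77% and about 93%. The 77% is the low end of that range and depends on the three assumptions set out above; it is not a consequence of the text. The point should be corrected, but it does not show that the trial is too small.

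**What to change.** - **Secondary outcomes:** state that the denominator is all randomised children in the arm, and that a child with no diary result for that week counts as not effective.
- **Statistical analysis:** take the effective rate out of the open list of missing-data methods for its main analysis, and keep listwise deletion and the other methods as sensitivity analyses.
- **Sample size:** label the 90% power at 79 per group as applying when drop-outs are excluded (not as assuming that there are none). Add that with all 88 per group in the denominator power runs from about 77% (90% and 70% are completer rates and all 10% drop-outs count as not effective, so 81% v 63%) to about 93% (90% and 70% are already whole-group rates), and say which case the anticipated rates represent.

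The cost is wording in three sections and a possibly less favourable stated power. Recruitment stays at 176. Trial status describes the study as still in therapist training, so at that stage the rule could be fixed before any outcome data were seen.

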### Inclusion criteria

Children aged 1–7 years.Children who meet the diagnostic criteria for functional constipation (Rome IV) [25, 26]. Must include 1 month of at least 2 of the following in infants up to 4 years of age: (1) 2 or fewer defecations per week; (2) history of excessive stool retention; (3) history of painful or hard bowel movements; (4) history of large-diameter stools; and (5) presence of a large fecal mass in the rectum. In toilet-trained children, the following additional criteria may be used: (6) at least 1 episode/week of incontinence after the acquisition of toileting skills and (7) history of large-diameter stools that may obstruct the toilet. For children over 4 years of age, there must include 2 or more of the following occurring at least once per week for a minimum of 1 month with insufficient criteria for a diagnosis of irritable bowel syndrome: (1) 2 or fewer defecations in the toilet per week in a child of a developmental age of at least 4 years; (2) at least 1 episode of fecal incontinence per week; (3) history of retentive posturing or excessive volitional stool retention; (4) history of painful or hard bowel movements; (5) presence of a large fecal mass in the rectum; and (6) history of large diameter stools that can obstruct the toilet.Parents or legal guardians are motivated to participate in the trial.Parents or legal guardians sign written informed consent.

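### A week without any stool leaves glycerine enema rate, stool form and distress with no value, the only printed rule for absent values would delete or replace that result, and the enema rate alone cannot show reduced enema use

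*Protocol article*

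**What the plan says.** Secondary outcomes in the protocol article: "The secondary outcomes are effective rate, stool form, distress sensation, and glycerine enema rate". Three of these four depend on a stool being passed.

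- **Enema rate:** "Glycerine enema rate is the times of using glycerine enema divided by the times of defecation, within a week".
- **Stool form:** the modified Bristol scale (m-BSFS) types feces from 1 (hard lumps) to 5 (watery). Table 3 has no category for no stool.
- **Distress:** "Distress sensation measured in the range of 0–3 represents the intensity of distress during defecation". The anchors run from no crying to hysterical crying, again with no category for no defecation.

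The fourth, effective rate, requires "on average, at least one bowel movement in 3 days, stool softening, defecate unobstructed". It keeps a value in a stool-free week, because the frequency part fails.

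Statistical analysis treats the first three as continuous variables, compared by t-test or Mann-Whitney test. Missing data are to be handled by "expectation maximization, last observation carried forward method or listwise deletion". The article does not mention a zero denominator or a completed diary week with no stool. The Discussion gives the purpose of the enema rate: a sign of difficult defecation and of whether the child can defecate unaided.

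**The concern.** Passing no stool all week is about the worst result a constipated child can record, and a completed diary observes it. On these three outcomes it has nowhere to go. If it falls under the printed missing-data rule, listwise deletion drops the child, LOCF substitutes a week in which stool was passed, and EM supplies a modelled score. Whether a value is absent depends on stool frequency, which is the primary outcome. The arm with fewer stools would then lose more of its most constipated children, and the comparison of form and distress would be between unlike subsets.

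A second, separate issue is the denominator of the enema rate. Treatment aims to raise the number of defecations, so the rate can fall because stools increased, because enemas decreased, or both. A reader who takes a lower rate as evidence of less enema use could be mistaken.

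**Working it through.** **The plan's own figures.** The article gives no stool means and no frequency of stool-free weeks, so there is no figure on this point to reproduce. Its sample size rests on the effective rate: the printed arcsine formula, with angles in degrees, returns 79.02 per arm, and 79 / 0.90 = 87.8, that is 88. Nothing below changes it.

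**1. What is defined in a week with no defecation** (from Secondary outcomes)

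| Outcome | Value |
|---|---|
| Enema rate | 0/0, or k/0 after k enemas without result: undefined |
| m-BSFS | no stool to type |
| Distress | no defecation to rate |
| Effective rate | defined: not effective |
| Weekly spontaneous bowel movements (SBMs, primary) | defined: 0 |

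**2. How often this might happen.** All means here are assumptions. Low stool frequency is one entry criterion among several, and any two suffice, so it is not required for entry.

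(a) Stools of any kind follow a Poisson count with mean m, so P(no stool) = exp(−m):

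| m per week | P(no stool) | Expected among 88 children |
|---|---|---|
| 1.5 | 22.3% | 19.6 |
| 2 | 13.5% | 11.9 |
| 3 | 5.0% | 4.4 |
| 4 | 1.8% | 1.6 |

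Arms at means of 2 and 4 would lack a value for about 14% vs 2% in a given week.

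(b) Each enema adds one stool that counts as a defecation. Assume 0.5 enemas per week in both arms, independent of spontaneous stools with means of 2 vs 4. Then P(no stool) = exp(−2.5) = 8.2% vs exp(−4.5) = 1.1%. A simulation of one million child-weeks per setting gave the same two figures.

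**3. Enema rate with enema use held fixed.** One enema per week divided by total defecations:

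- 2 defecations: 1/2 = 50%
- 3 defecations: 1/3 = 33%
- 5 defecations: 1/5 = 20%

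From 3 to 5 defecations the relative change is (20 − 33.3)/33.3 = −40%, with no change in enemas. If the assisted stool is added to 2 or 5 spontaneous stools, the rate is 1/3 = 33% vs 1/6 = 17%, the same direction. In setting (b), the mean rate among children with a value is 0.20 vs 0.11 although both arms average 0.5 enemas.

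**4. Direction.** The denominator effect lowers the enema rate in the arm with more stools. Listwise deletion of stool-free weeks removes more poor results from the arm with fewer stools. For the enema rate the first favours the arm with more stools and the second favours the other, and the documents do not allow a net sign to be computed.

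**The case against.** The enema rate answers the question that the Discussion sets. One assisted stool in two and one in five are different results if the question is how often the child manages alone, and a fall with more unaided stools is then intended. This stands. A reader might infer that the rate is invalid, or that it improperly counts the primary outcome twice. The documents do not support that: the article nowhere offers the rate as evidence independent of stool frequency, and overlap between a secondary and a primary outcome is ordinary.

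Coding of a stool-free week is often left to an analysis plan, which is not shown, and the article does not say in terms that such a week counts as missing. This stands in part. However, the definitions and the missing-data rule are both printed, and as printed nothing else covers an absent value.

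A reader might also take 14% vs 2% as the expected loss. It is one assumed setting. The enema definition counts defecations without restricting them to spontaneous ones. If assisted stools count, undefined weeks are rarer, and rarer still if enemas go mainly to children who are not passing stool.

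Nor can it be said that the substituted value is always better, since LOCF may carry forward a poor baseline score. The child is also not lost to the trial, because weekly SBMs and the effective rate still register the week.

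Finally, a simple remedy has faults of its own. A raw enema count gives a child with no stool and no enema a 0, the best score. The m-BSFS is abnormal at both ends, so assigning a type to a stool-free week would invent an observation.

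**Conclusion.** The gap is real and limited to secondary outcomes. Three of four have no value in a stool-free week, and the only rule printed for absent values would delete or replace an observed result, to a different extent in each arm if stool frequency differs. Under the Poisson assumptions the share of affected child-weeks is about 14% vs 2% (2 vs 4 stools of any kind) or about 8% vs 1% (2 vs 4 spontaneous stools plus 0.5 assisted). The true frequency is unknown.

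Separately, the enema rate is a sound share of stools that needed help, but alone it cannot show reduced enema use: 33% vs 20% can arise with one enema per week in both arms.

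It would go too far to say that the enema rate is biased in a known direction, since the two effects oppose each other. The primary outcomes and the sample size are untouched.

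**What to change.** 1. Keep the enema ratio and state whether an enema-assisted stool counts in its denominator.
2. Add enemas per week, which is the ratio's numerator and is defined for every child. Read it together with weekly SBMs, because no stool and no enema also scores 0.
3. State that a completed diary week without a stool is an observed result, not to be imputed or deleted as missing data.
4. Report the number of such weeks per arm.
5. Compare stool form and distress among weeks with a stool. Alongside, run one Mann-Whitney sensitivity analysis that ranks stool-free weeks as less favourable than every observed outcome, without giving them an m-BSFS type or a distress score.

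The cost is wording, one extra outcome summary and one sensitivity analysis with a ranking convention that must be stated. No new data are needed, as the diary already covers stools and enemas. Trial status places the study at therapist training, so this can be settled before outcome data are seen.
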